## Abstract

**Background:** Burn patients experience major physiological and psychological stressors during treatment and rehabilitation, including elevated levels of pain, anxiety, stress, or depression. Music interventions inclusive of music therapy (MT) have been shown to improve such symptoms, but rigorous clinical trials investigating specific music therapy methods in adult burn patients are scarce.

**Methods:** This is a single center Randomized Controlled Trial (RCT) protocol with two parallel arms. Participants are 81 adult burn patients admitted to the Intensive Care Unit (ICU) of the University Hospital Fundación Santa Fe de Bogotá in Colombia. The intervention consists of a Music Assisted Relaxation (MAR) protocol, a music therapy technique composed of entrained live music combined with a guided relaxation and/or the use of imagery. The effects of the MAR will be compared to a control group (treatment as usual) over a period of maximum 2 weeks or six interventions. The primary outcome measure is perceived background pain, as measured with a Visual Analog Scale (VAS) before and after each intervention. Secondary outcomes are anxiety and depression levels; vital signs; and the use of pain medication. Additionally, some patients in the intervention group will be invited to participate in electroencephalography, electromyography, and electrocardiography recordings during the MAR.

**Discussion:** This study protocol follows the SPIRIT guidelines for defining items of clinical trials and is the first study in Colombia to evaluate the effects of music therapy for adult burn patients. With this RCT it is hoped to gather new knowledge about the potential of music therapy to help critical care patients cope and recover from their injuries during the hospitalization in the ICU.

**Trial registration:**
www.clinicaltrials.gov, Identifier: NCT04571255.

**Protocol version:** V1.0, May 24th 2021

## Introduction

Burn wounds are among the most painful and traumatic injuries that a person can experience and provide multiple challenges for both patients and health care professionals (1). Effective fluid resuscitation, preventing burn shock, and recovering cardiovascular and metabolic balance are some of the initial priorities for burn patients in the Intensive Care Unit (ICU) (2, 3). Early wound healing and the restoration of skin tissue are further medical procedures on which the success for survival and recovery depend on (4). Pain is a symptom that accompanies burn patients during all phases of treatment and rehabilitation and successful pain management is key to both physical and mental health (5). In the ICU, the evolution and trajectory of pain in burn patients is difficult to predict, and frequently the pain is intense and persistent (6, 7). Pain in burn patients can be categorized according to four types (8):

First, the background pain resulting from the injuries and the destruction of skin tissue. Many times, this pain is of moderate or low intensity, but usually remains over time.Second, many patients experience intense procedural pain during medical and therapeutic procedures, such as wound debridement, dressing change, or during physical therapy, among others.Third, breakthrough pain, which can occur at any time.And fourth, the post-operative pain that is associated with wounds caused by skin extraction and grafting.

It is widely recognized that pain perception is based on an individual experience that affects the patient's physiological, mental, emotional, and social aspects of life (9). The International Association for the Study of Pain (IASP) defines pain as “an unpleasant sensory or emotional experience associated with actual or potential tissue damage, or described in terms of such damage” and concludes that "pain is always subjective” (10). Consequently, biopsychosocial models in treating pain in burn patients have been put forward (11, 12).

Additionally, there are also psychological challenges that burn patients must face, such as elevated levels of anxiety, stress, depression, insomnia, and changes in body identity (13). This is important, since pain perception is mediated by psychological distress in the short- and long term (14–17). One study found that 68.5% of burn patients still experience moderate pain and 42.1% live with high levels of anxiety and depression 1 year after hospital discharge (18). An adequate pain management is therefore paramount for burn patients and leads to a better recovery and overall quality of life (19). Pharmacological treatment is usually the main pillar of pain management in burn patients, but complementary therapies are widely used and recommended (20, 21). Music therapy (provided by a credentialed music therapist) and music medicine (provided by other health care professionals) interventions have been used in critical care for many years, and positive physiological and psychological effects have been reported across an array of populations (22–26). Pain is a frequently used outcome measure in different medical settings and recent reviews confirm the effectiveness of music interventions in reducing pain levels (27–29). For burn patients, a former meta-analysis showed positive effects on pain, anxiety, and heart rate (30) and a more recent systematic review and meta-analysis found statistically significant effects for pain, anxiety, and relaxation levels (31). However, most studies with adult burn patients focus on recorded music listening protocols for procedural pain, indicating a lack of RCTs investigating live music approaches for other types of pain. Non-procedural pain in adult burn patients was investigated only in two previous studies, both of which applied recorded music via an MP3 player for 20 min, once a day, for three consecutive days (32, 33). Three RCTs were found that used live music approaches, but two of them were conducted with pediatric patients (34, 35) and one with both pediatric and adult participants (36). In general, receptive music interventions such as music guided/assisted relaxation or distraction techniques, are much more common in burn patients compared to active music therapy experiences.

This study protocol aims at filling some of the current gaps in knowledge by measuring the effects of a live Music Assisted Relaxation (MAR) protocol—provided by a certified music therapist—on background pain, mental health, vital signs, and the use of pain medication in adult burn patients.

## Objectives

The primary objective of this study is to evaluate the effect of a MAR protocol compared to treatment as usual on perceived background pain in adult burn patients admitted to the Intensive Care Unit of the University Hospital Fundación Santa Fe de Bogotá.

Secondary objectives are:

To examine the effects of the MAR on the patients' anxiety and depression levels.To examine the effects of the MAR on the patients' vital signs (heart rate, respiratory rate, oxygen saturation, blood pressure).To examine the effects of the MAR on the patients' medication usage (complementary or rescue doses).To examine medical and social factors, which might be associated with the effects of the MAR.To describe the effects of the MAR on neurophysiological parameters in a few patients in the intervention group (exploratory part of the study).

We hypothesize that the MAR protocol plus treatment as usual—as compared to treatment as usual alone—will lead to lower levels of perceived background pain and will positively impact the patients' mental health, vital signs, and medication usage.

## Methods and Analysis

### Study Design and Setting

This study protocol follows the SPIRIT guidelines for defining standard protocol items for clinical trials (37). This study is a single center Randomized Controlled Trial (RCT) with two parallel arms (38) and takes place at the Adults Intensive Care Unit of the University Hospital Fundación Santa Fe de Bogotá (FSFB), Colombia. Figure 1 shows the flow-diagram of the study (39).

**Figure 1 F1:**
[figure not shown]
Flow-diagram. Flow-diagram adapted from Schulz et al. (34). VAS, Visual Analog Scale; MAR, Music Assisted Relaxation; TAU, Treatment as usual; EEG, Electroencephalography; ECG, Electrocardiography; EMG, Electromyography; ITT, Intention-to-treat.

### Inclusion Criteria and Exclusion Criteria

Inclusion criteria are burn patients of legal adult age admitted to the ICU of the University Hospital Fundación Santa Fe de Bogotá; and an estimated hospitalization of >7 days. Exclusion criteria are patients with known psychiatric disorders; patients with cognitive disabilities; and sedated and/or mechanically ventilated patients.

### Participants and Sample Size Calculation

The sample size was calculated according to the Asymptotic normal method (40). Obtaining a power of 80% and taking a *p*-value of 5%, the number of participants expected to have in the study is *n* = 81, which is similar to other studies in the field (30, 31). The formula used for calculating the sample size (40, 41) is:

$$\begin{array}{l} n=\frac{{\left[Z\left(\alpha /2\right)\sqrt{\left(2P\left(1-P\right)\right)}+Z\left(\beta \right)\sqrt{\left(P1\left(1-P1\right)+P2\left(1-P2\right)\right)}\right]}^{2}}{{\left(P1-P2\right)}^{2}} \end{array}$$

Where *P* = 0.5^*^(P1 + P2), Power = 1-β and Z(α/2) and Z(β) are taken from the z table. For this particular case, P1 corresponds to the expected outcome in the control group and P2 the expected outcome in the intervention group. The primary outcome measure is the Visual Analog Scale (VAS) that consists of 10 points (100%) and when considering a clinically significant decrease and difference of 2 points (20%), these values would correspond to 80 and 60%, respectively (P1: 80 and P2: 60). Replacing these values in the above equation, the sample size is:

$$\begin{array}{l} n=\frac{{\left[1.96\sqrt{\left((2.07)*(1.07)\right)}+0.842\sqrt{\left(0.8*(1-0.8)+0.6*(1-0.6)\right)}\right]}^{2}}{{\left(0.2\right)}^{2}}\\ \;=81.25\;\approx \;81 \end{array}$$

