### Randomization and Group Allocation

Randomization takes place in the form of assigning the participants according to a set of randomized numbers generated by a computer software (Excel 2020, Microsoft Cooperation). The randomization ratio is 1:1. Once randomization is executed, sealed envelopes are used for each participant and group allocation is performed accordingly.

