### Other Outcome Measures

In about 20% of the patients in the intervention group (approx. eight participants), additional Electroencephalogram (EEG), Electrocardiogram (ECG) and Electromyography (EMG) recordings will be made. Since this is an exploratory feature of the study, participation in the EEG, ECG, and EMG measurements is voluntary and depends on the location of the burn wounds, the clinical stability of the patient, and is defined together with the attending physician. The sample size of 20% was chosen based on an estimation of potential participants without any head/face/neck burn injuries, in which the application of electrodes would not be feasible. As the aim of the MAR is to help patients achieve relaxation, the hypothesis for these measurements is that this will lead to (1) an increase in Alpha and Theta brain waves, both of which correspond to deep relaxation and inward-focused states of mind; (2) a reduction in muscular tone; and (3) changes in the high frequency (HF) and low frequency (LF) components and in the LF/HF ratio indicating a parasympathetic activation. All these physiological variables will be acquired simultaneously with a Micromed LTM64 (Micromed S.P.A., Italy) acquisition system, with a sampling frequency of 512 Hz. The Micromed LTM64 is of clinical quality and has the due approval of the Colombian National Institute for Drug and Food Safety (20090486-2015). For the EEG recordings, the international 10-20 scalp system setup will be used, but the final number of electrodes will depend on medical approval for each patient. From these signals, we will assess power changes in the physiological Theta (4-8 Hz), Alpha (8-12 Hz) and Beta (12-30 Hz) frequency bands, associated with brain relaxation and engagement, respectively (46, 47). The ECG will be acquired using the lead II bipolar montage with two electrodes located bilaterally in the upper chest or both arms depending on the possibilities or limitations of each patient and on his/her medical condition. From the ECG we will measure changes in heart rate and Heart Rate Variability (HRV) associated with the intervention. For this last, we will assess contributions from the sympathetic and parasympathetic branches of the autonomic nervous system through the LF and HF components from the spectral analysis of the tacogram (48). The EMG will be recorded to evaluate changes in muscular tone associated with the intervention, using a bipolar montage with two electrodes located in the chin (when possible). Muscular tone activations will be assessed through changes in amplitude of the EMG signal.

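### The sample size formula gives 81.25 patients per group, but 81 is used as the total for both arms, so the calculation shown does not support the stated 80% power

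*Protocol article*

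**What the plan says.** The section Participants and Sample Size Calculation sets 80% power at the 5% level and prints the normal-approximation formula for two independent proportions. It explains that "P1 corresponds to the expected outcome in the control group and P2 the expected outcome in the intervention group". A 2-point difference on the 10-point VAS is recast as 20%, and "these values would correspond to 80 and 60%, respectively (P1: 80 and P2: 60"). The worked line ends in 81.25, rounded to 81, and the text concludes that "the number of participants expected to have in the study is *n* = 81".

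Three other places show that 81 is meant as the whole trial:

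- The Abstract describes two parallel arms and says "Participants are 81 adult burn patients admitted to the Intensive Care Unit (ICU").
- Randomization and Group Allocation says "The randomization ratio is 1:1".
- Other Outcome Measures plans extra recordings "In about 20% of the patients in the intervention group (approx. eight participants").

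No section says 81 per arm or doubles the result of the formula.

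**The concern.** In the printed formula, n is the number in each of the two groups. If that figure is enrolled as the total, each arm has half the patients the calculation calls for, and the power attached to the calculation no longer applies. What is at stake is the justification of the trial's size. This is the only power calculation in the document, and readers of the results will take 80% from it when they judge a non-significant finding on background pain.

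**Working it through.** **Inputs, all from the sample size section unless noted.** P1 = 0.80 (control), P2 = 0.60 (intervention), so P = 0.5 × (0.80 + 0.60) = 0.70. Z(α/2) = 1.96, hence two-sided 5%. Z(β) = 0.842, hence 80% power. Allocation is 1:1 (Randomization and Group Allocation).

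**Step 1: reproduce the protocol's figure.**

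- First term: 1.96 × √(2 × 0.7 × 0.3) = 1.96 × 0.6481 = 1.2702
- Second term: 0.842 × √(0.16 + 0.24) = 0.842 × 0.6325 = 0.5325
- n = (1.2702 + 0.5325)² / 0.2² = 3.2499 / 0.04 = 81.25

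This matches the document. The worked line prints (2.07)*(1.07) where 2(0.7)(1−0.7) is meant. Only the latter gives 81.25, so the correct value was used and the slip is typographical.

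**Step 2: per group or total?** With n patients in each arm, the variance of the difference in proportions is [P1(1−P1) + P2(1−P2)] / n. The formula uses exactly this sum, without a factor for splitting n between two arms, so n is per group. Inverting it confirms this:

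Power = Φ( [0.2 × √n − 1.96 × 0.6481] / 0.6325 )

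- n = 81 in each arm: (1.8000 − 1.2702) / 0.6325 = 0.838, power 79.9%
- n = 82 in each arm: (1.8111 − 1.2702) / 0.6325 = 0.855, power 80.4%

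The 80% claim therefore goes with 81 to 82 per arm. Rounded up, the requirement is 82 per arm, or 2 × 82 = 164 in total.

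**Step 3: the arm size the protocol plans.** 81 / 2 = 40.5 per arm. Independently, about eight patients at 20% implies 8 / 0.20 = 40 in the intervention arm. With 81 per arm, 20% would be about 16.

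**Step 4: power at that size, same inputs.**

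- n = 40.5 per arm: (0.2 × 6.3640 − 1.2702) / 0.6325 = 0.004, power 50.2%
- 40 per arm gives 49.7%, 41 per arm gives 50.7%, and a 40/41 split gives 50.1% to 50.3%
- Exact binomial enumeration at 40/41 gives 51% to 52% for the uncorrected chi-square test and 44% to 47% for Fisher's exact test

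**Step 5: could another convention explain 81 in total?** The unpooled-variance form gives 78.5 per group, a one-sided 5% test 64, and the continuity-corrected form 91. None corresponds to 81 in total. A one-sided test at 40.5 per arm would have 62.8% power.

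**Step 6: power for a difference in VAS scores.** The document gives no SD, so the values below are assumptions. For a 2-point difference at 40.5 per arm, √(2/40.5) = 0.2222 and

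Power = Φ( 2 / (SD × 0.2222) − 1.96 )

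| Assumed SD | 2 / (SD × 0.2222) | Power |
|---|---|---|
| 2 | 4.50 | 99% |
| 3 | 3.00 | 85% |
| 4 | 2.25 | 61% |
| 4.5 | 2.00 | 52% |

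Power reaches 80% at an SD of 2 / [(1.96 + 0.842) × 0.2222], about 3.2 points.

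**The case against.** The strongest reply is that the binary calculation does not describe the trial's analysis. The primary outcome is a 0–10 score, and Data Management and Statistical Analysis names ANOVA, the t-test and the Mann-Whitney test for pain. No responder endpoint is defined. Treating 0.80 and 0.60 as proportions is equivalent to every patient scoring 0 or 10: the SDs would be 10 × √0.16 = 4.0 and 10 × √0.24 = 4.9, or √20 ≈ 4.5 when averaged on the variance scale. At a smaller spread, 81 patients could be enough for a 2-point difference.

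This objection stands, and it limits the conclusion. A reader might infer that the trial's true power is 50%, or that it has an even chance of missing a 2-point effect. The document does not support either statement: both hold only for a comparison of 80% with 60%. The objection does not rescue the stated 80%, however, because that figure comes from the binary calculation and was reached by using a per-group number as a total. That 81 might suffice under some SD is possible, but the document does not show it.

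A second reply is that the Discussion calls this a feasibility study. The sample size section nevertheless claims 80% power, and the Objectives state an efficacy hypothesis on pain, so the claim has to be right. Nor is this a detail left to a fuller document: the calculation is given here and its result is misapplied here.

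**Conclusion.** The point holds in a bounded form. The formula returns 81.25 per group (82 per arm, 164 in total), while the protocol uses 81 as the total, about 40 per arm. On the protocol's own inputs (80% versus 60%, two-sided 5%, 1:1) the power of 81 patients is about 50%, so the stated 80% is not supported by the calculation given. The error in the group size is a factor of two, and it is demonstrable from the document alone.

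Power for the planned VAS score analysis is undetermined, because no SD is stated. It would exceed 80% if the SD were below about 3.2 points and fall short if it were above. These figures assume a 2-point difference in means, a normal approximation and all 81 patients analysed. Rounding 81.25 down and the misprinted substitution are minor and do not affect the conclusion.

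**What to change.** In Participants and Sample Size Calculation:

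1. State that 81.25 is the number per group, and withdraw the 80% power claim for 81 in total.
2. Preferably, replace the calculation with the power for a difference in mean VAS at 40/41 per arm, using a stated SD with its justification. This matches the score analysis planned for pain.
3. If the binary basis is kept, state the power as about 50% for 80% versus 60%, and say that it refers to that comparison only.
4. Correct the substituted term to 2(0.7)(1−0.7), as a typographical correction.

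The cost is the rewording of one paragraph and the work of finding a defensible SD. The stated power may become less favourable. Correcting the statement does not itself require more patients.

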### Primary Outcome Measure

Primary outcome measure is a Visual Analog Scale (VAS) of 0-10. 0 indicates a state without any pain and 10 indicates the most severe pain possible. Each number from 0 to 10 is distributed in a line 1 cm apart and the patient can mark the intensity of pain felt at the time of filling out the VAS. The VAS will be applied at baseline, and every time before, after, and at 3 h post-each intervention. Period of data collection: maximum 2 weeks from the point of study entry.

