
While it is known that music itself can release neurotransmitters and hormones related to pain and stress relief (66), the trauma that many burn patients experience and the inherent link between pain and mental health requires the presence of credentialed professionals, such as music therapists. Profound relaxation can help in self-regulation but may sometimes evoke undesired emotions or thoughts. Stressing the importance of the therapeutic relationship applies also for this study, and time for verbal processing after the MAR will be used to elaborate the experiences during the intervention. While the length of the ICU stay for burn patients can fluctuate, we tried to offer a process-oriented protocol with a maximum of six interventions over the course of 2 weeks. This may not seem a lot, but to our knowledge, all other RCTs on music or music therapy interventions used single interventions or interventions over a few consecutive days) (30, 31).

Another new feature of this study is the focus on background pain instead of procedural pain. While background pain is usually lower in intensity, it is of longer duration and may thus alter pain memory in the long-term (6). This is important, since pain chronification may increase the already higher risks of burn patients in developing mental health impairments, such as acute stress disorder (ASD), post-traumatic stress disorder (PTSD), elevated stress levels, depression, and insomnia (6, 67). Especially in times of an ongoing opioid crisis, complementary treatments to pharmacological strategies for pain management in burn patients are needed not only for procedural pain, but also for background pain (68). In a previous meta-analysis of music interventions and pain in different medical settings, Lee (28) found a statistically significant reduction in opioid intake. However, in the three RCTs found with adult burn however, this result has not been replicated (33, 69, 70). In this study protocol we will try to evaluate total opioid intake during the intervention period, specifically in relation to rescue doses requested by the patients.

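### The sample size comes from a two-proportion formula applied to a rescaled 0-10 pain score, so the stated 80% power is not tied to the planned comparison of scores

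*Protocol article*

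**What the plan says.** The section Participants and Sample Size Calculation prints the normal-approximation formula for two independent proportions, with variance terms of the form P(1-P), two-sided 5% significance and 80% power. It defines the inputs as follows: "P1 corresponds to the expected outcome in the control group and P2 the expected outcome in the intervention group". It treats the 10 points of the VAS as 100% and continues: "when considering a clinically significant decrease and difference of 2 points (20%), these values would correspond to 80 and 60%, respectively". The result is 81.25, taken as 81.

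The abstract gives 81 as the number of participants in the trial. Randomization and Group Allocation sets a 1:1 ratio. Other Outcome Measures equates about 20% of the intervention group with about eight patients, which implies about 40 per arm.

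Primary Outcome Measure defines pain as a score on a 0-10 line, where "0 indicates a state without any pain and 10 indicates the most severe pain possible". Data Management and Statistical Analysis compares pain by ANOVA and Mann-Whitney, and quantitative variables by t-test or Mann-Whitney. No SD for the VAS, no VAS cut-off and no responder definition appears anywhere.

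**The concern.** A pain score divided by 10 is not a fraction of patients, and P(1-P) is not its variance. The formula answers a question about how many patients have an event, and the protocol defines no event. The power of a comparison of scores depends on the between-arm difference relative to the SD, and no SD enters the calculation.

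There is a second mismatch. The formula returns the number needed in each arm, but the article uses the result as the trial total.

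What is at stake is the only formal justification for the size of the trial. As written, a reader cannot tell what mean difference 81 patients can detect, and a null result could not be read against the stated 80%.

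**Working it through.** **Inputs from the article.** Two-sided 5% (z = 1.96); 80% power (z = 0.842); P1 = 0.80; P2 = 0.60; target difference 2 VAS points; 81 in total at 1:1, so 40 versus 41. The SD is not given, so every SD from step 4 on is an assumption, shown over a range.

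**1. Reproducing the article's figure.** With P = 0.5 × (0.8 + 0.6) = 0.7:

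- 1.96 × √(2 × 0.7 × 0.3) = 1.96 × √0.42 = 1.270
- 0.842 × √(0.8 × 0.2 + 0.6 × 0.4) = 0.842 × √0.40 = 0.533
- n = (1.270 + 0.533)² / 0.2² = 3.250 / 0.04 = 81.25

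The figure reproduces, as n **per arm**. Taken literally, the printed term (2.07)*(1.07) would give about 297; only 2 × 0.7 × (1 − 0.7) gives 81.25.

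**2. What that n delivers on the article's own terms.** Solving the same formula for power, z = (0.2√n − 1.270) / √0.40:

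- 81 per arm: z = 0.838, power 79.9%
- 40.5 per arm (81 in total): z = 0.004, power about 50%

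**3. The SD hidden in the formula.** The two variance terms are 0.16 and 0.24. On the 10-point scale these are SDs of 10√0.16 = 4.0 and 10√0.24 = 4.9. Their average variance of 0.20 gives 10√0.20 = 4.47 points. For means of 8 and 6 on a 0-10 scale, SDs that large occur only if every patient scores exactly 0 or 10.

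**4. Power for a comparison of mean scores.** Two-sided 5% t-test at a single time point, 40 versus 41, noncentral t, difference of 2 points:

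| Assumed SD | Power, 81 in total | n per arm for 80% power, t-test | n per arm for 80% power, normal approximation |
|---|---|---|---|
| 2.0 | 99% | 17 | 16 |
| 2.5 | 94% | 26 | 25 |
| 3.0 | 84% | 37 | 36 |
| 3.5 | 72% | 50 | 49 |
| 4.0 | 60% | 64 | 63 |

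The normal approximation is n per arm = 2(1.96 + 0.842)² × SD² / 2². At SD 3.0 this is 15.70 × 9 / 4 = 35.3, so 36.

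**5. Break-even.** With 40 versus 41, 80% power corresponds to a standardised difference of 0.63. For 2 points the SD may then be at most 2 / 0.630 = 3.17, or about 3.2.

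**6. Cross-check.** At the formula's implied SD of 4.47, the t-test has 51% power with 40 versus 41 and 81% with 81 per arm. The gap between 50% and 80% in step 2 therefore comes from using a per-arm number as the total.

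**The case against.** The strongest defence is that the number may be adequate even though its derivation is not. The table straddles 80%, and an SD of about 3.2 or less gives at least the stated power for 2 points. That stands: no shortfall is demonstrated. It does not rescue the stated 80%, which would then be right only by coincidence with an SD that the article never states.

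A second defence is that the analysis section also names chi-square and logistic regression, which suit a binary outcome. This fails. Chi-square follows a sentence on qualitative variables, logistic regression is a final multivariate step, and neither comes with a binary pain outcome.

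A third is that a single-time-point t-test is not the planned analysis either. The VAS is taken at baseline and around each of up to six sessions, and Mann-Whitney is allowed. This stands: repeated measures or baseline adjustment would change the figures, so those above are conditional.

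Stronger readings are tempting, but the documents do not support them:

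- **That the printed (2.07)*(1.07) makes the sample size wrong.** The other terms are correct and the intended expression gives exactly 81.25. It is a typesetting slip.
- **That a control level of 8 out of 10 contradicts the protocol.** The Introduction says of background pain "Many times, this pain is of moderate or low intensity", and the Discussion adds "While background pain is usually lower in intensity, it is of longer duration". These statements are qualified, and the Introduction also describes burn pain in the ICU as frequently intense. That is tension, not contradiction. The article also never writes mean scores of 8 and 6; that reading is inferred from its mapping of 10 points to 100%. No control mean enters a two-means formula.
- **That the trial has low power for smaller effects, such as 1 point.** The article sets 2 points and no other target.
- **That the wording on decrease and difference confuses change within patients with a contrast between arms.** P1 and P2 are defined as control and intervention, so the contrast used is between arms.

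**Conclusion.** The point holds. The calculation uses a method for proportions on a score outcome, uses no SD, and takes a per-arm number as the total. The stated 80% power belongs neither to the planned test nor, at 81 in total, to the article's own two-proportion inputs, where it is about 50%.

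A reader might infer that the trial is underpowered, or conversely that 81 can simply be kept. Neither follows. The two errors pull in opposite directions: the implied SD of about 4.5 pushes n up, and reading a per-arm number as a total halves it. Whether 81 is enough for 2 points turns on the SD: yes up to about 3.2, no above it. This rests on a two-sided 5% t-test at one time point, 40 versus 41 patients analysed, and assumed SDs, because the article gives none.

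**What to change.** Replace the two-proportion calculation with a two-means calculation, or a baseline-adjusted one, for a 2-point between-arm difference in mean VAS at a named time point. State and justify the SD, and label n per arm and in total. Remove the conversion of points into 80% and 60%. If a proportion is really intended, define the responder and make that comparison the primary analysis.

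Then restate what 81 in total delivers: for a single-time-point, two-sided 5% t-test, 80% power for a standardised difference of 0.63, that is, for 2 points only if the SD is at most about 3.2. If the justified SD is larger, state the lower power (for example 72% at 3.5 or 60% at 4.0). Correct the printed (2.07)*(1.07) as a copy-edit. No control mean is needed.

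The cost is one rewritten paragraph and a source for the SD. If that SD is about 3.2 or less, the rewrite itself requires no change in enrolment. If it is larger, the further cost is stating that power is below 80% or, to keep 80%, recruiting more patients: 100 in total at SD 3.5 from the t-test column above.

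### The sample size takes 8/10 as the expected control pain score without a source, which does not fit the protocol's account of background pain and leaves the 2-point target difference unsupported

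*Protocol article*

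**What the plan says.** All figures are in the protocol article.

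- **Participants and Sample Size Calculation.** The aim is "Obtaining a power of 80" per cent at a 5% level, with a two-sided critical value ("Z(α/2) and Z(β) are taken from the z table"). The inputs are defined thus: "P1 corresponds to the expected outcome in the control group and P2 the expected outcome in the intervention group". The scale is converted to a percentage: "The primary outcome measure is the Visual Analog Scale (VAS) that consists of 10 points (100" per cent). A 2-point difference becomes 20 percentage points, and "these values would correspond to 80 and 60%, respectively (P1: 80 and P2: 60"). The result is 81.25, rounded to 81. No source is given for the control value, and no SD.
- **Introduction**, on background pain: "Many times, this pain is of moderate or low intensity, but usually remains over time".
- **Discussion**, contrasting it with procedural pain: "While background pain is usually lower in intensity, it is of longer duration".
- **Inclusion Criteria and Exclusion Criteria**: "Inclusion criteria are burn patients of legal adult age admitted to the ICU", with an expected stay of more than 7 days. No pain score is required.
- **Trial size.** The Abstract gives 81 patients in all, and the randomization section a 1:1 ratio. Under Other Outcome Measures, 20% of the intervention arm is about eight patients, so an arm holds about 40.

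**The concern.** The primary outcome is background pain. The calculation expects controls to score 8 out of 10 on it, while the rest of the article describes it as often moderate or low. Nothing in the entry criteria would select patients with high scores.

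The starting level matters for judging the target. Two points is 25% of 8, but 40% of 5, 50% of 4 and 67% of 3, and a patient who scores 0 or 1 cannot improve by 2. If the achievable difference is smaller than planned, a null result could be read as absence of effect when the trial had little chance of showing one.

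**Working it through.** **1. Reproduce the plan's figure.** Inputs: P1 = 0.80, P2 = 0.60, P = 0.70, z-values 1.96 and 0.842.

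- 1.96 × √(2 × 0.70 × 0.30) = 1.96 × 0.6481 = 1.2702
- 0.842 × √(0.80 × 0.20 + 0.60 × 0.40) = 0.842 × 0.6325 = 0.5325
- n = (1.2702 + 0.5325)² / 0.20² = 3.2499 / 0.04 = 81.25

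This matches. The printed first term works only if read as 2 × 0.7 and 1 − 0.7; taken literally it gives 297. In this formula n is the number per arm.

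**2. Keep the 2-point difference and lower the control level.** Power for n per arm is Φ{[√n × |P1 − P2| − 1.96√(2P(1−P))] / √(P1(1−P1) + P2(1−P2))}.

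| Control → MAR | n per arm (formula) | Power, 81 per arm | Power, 40.5 per arm |
|---|---|---|---|
| 8 → 6 | 81.2 | 80% | 50% |
| 7 → 5 | 93.0 | 74% | 45% |
| 6 → 4 | 97.0 | 73% | 44% |
| 5 → 3 | 93.0 | 74% | 45% |
| 4 → 2 | 81.2 | 80% | 50% |
| 3 → 1 | 61.6 | 90% | 62% |

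The level has little influence. 4 versus 2 gives exactly the same n as 8 versus 6, because p(1−p) is symmetric about 0.5. The last column applies to this trial, since 81 is the total.

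**3. Compare means instead.** Here n per arm = 2 × (1.96 + 0.842)² × SD² / d² = 15.70 × SD² / d². The control level does not appear. For d = 2 and an assumed SD of 2, 2.5 or 3 (the article gives none), n = 15.7, 24.5 or 35.3, that is 16, 25 or 36 per arm.

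**4. Let the difference shrink.** Suppose, as an assumption only, that the benefit is proportional. The move from 8 to 6 is a 25% reduction, so control levels of 5, 4 and 3 give 1.25, 1.0 and 0.75 points. Power of a two-sided 5% t-test with 40 per arm:

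| Difference | SD 2 | SD 2.5 | SD 3 |
|---|---|---|---|
| 2.0 | 99% | 94% | 84% |
| 1.25 | 79% | 60% | 45% |
| 1.0 | 60% | 42% | 31% |
| 0.75 | 38% | 26% | 20% |

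**5. Floor of the scale.** I simulated rounded 0–10 scores with 40 per arm, subtracting 2 points in one arm and truncating at 0. With SD 2.5, the share scoring 0 or 1 is about 16% at mean 4 and 27% at mean 3. The average fall at mean 3 drops to about 1.6 points. Truncation also reduces the variance, so t-test power is still about 92% at mean 3 with SD 2.5, and about 80% in the least favourable case tried (mean 3, SD 3). The floor alone therefore does not defeat a nominal 2-point effect.

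**The case against.** **The target is absolute.** The article plans a difference of 2 points and nowhere plans a 25% relative benefit. A reader might put that reduction into the printed formula, obtain about 246, 356 or 539 per arm at control levels 5, 4 and 3, and conclude that the 80% power is void because of the pain level. The documents do not support this: they do not say that the effect scales with baseline pain, and at the planned 2 points the level barely matters. This stands, and it limits the point to the plausibility of the inputs.

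**The conflict is one of description.** The Introduction's wording covers many cases, not all, and includes moderate pain. The Discussion's comparison is relative to procedural pain and carries no score. The Introduction also says that pain in burn patients in the ICU is frequently intense, though of burn pain in general. The 8/10 follows from the percentage conversion and is not stated as a score. All this is fair; it makes the mismatch less than a flat contradiction. It does not supply a basis for 8/10.

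**The article already admits uncertainty.** Potential Limitations says that many factors affect background pain and that broad inclusion may affect power. It does not discuss the control value or the target difference.

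**Conclusion.** The point holds in a limited form. An expected control score of 8/10 is unsourced and does not fit the article's own description of background pain or its entry criteria. This does not by itself invalidate the 80% power. It does leave the 2-point difference without support at the pain levels the article describes.

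How much that matters depends on the true difference and the SD, neither of which the documents settle. At 2 points, a t-test with 40 per arm has 84% to 99% power for SDs of 3 down to 2. At 0.75 to 1.25 points it has 26% to 60% at SD 2.5, and 20% to 79% over SDs of 2 to 3. The SDs, the 25% reduction and the control levels of 3 to 5 are assumptions made here.

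A separate fault bears on any restatement. The formula's 81 is per arm but is used as the total. With 40 to 41 per arm, the article's own 80% and 60% give about 50% power, and control levels from 3 to 8 give about 44% to 62%. The article's formula therefore does not yield 80% at the actual arm size at any of these levels.

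**What to change.** In Participants and Sample Size Calculation:

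1. Justify the 8/10 control value, or replace it with the background-pain level expected in this ICU, with its source (for example the hospital's own records).
2. Justify the target difference at that level.
3. Restate the power with a calculation for a mean score, using the actual 40 to 41 per arm, over a stated range of differences and SDs. Do not carry 81 per arm into the restatement.
4. If the range includes differences of about 1 point, say that the trial may not detect them.

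The cost is one rewritten paragraph and a short recalculation. This point requires no change to enrolment or procedures. The downside is that the stated power may become less favourable.
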